## Abstract

**Background:**

Depression in older adults has serious biological, psychological, and social consequences. Homebound older adults experience a high burden of depression and significant barriers to accessing mental health treatments. Few interventions to address their specific needs have been developed. Existing treatment modalities can be challenging to scale up, are not tailored to unique population concerns, and require significant staffing support. Technology-assisted, layperson-facilitated psychotherapy has the potential to overcome these challenges.

**Objective:**

The aim of this study is to assess the efficacy of a layperson-facilitated internet-delivered cognitive behavioral therapy program tailored for homebound older adults. The novel intervention, Empower@Home, was developed based on user-centered design principles and partnerships between researchers, social service agencies, care recipients, and other stakeholders serving low-income homebound older adults.

**Methods:**

This 2-arm, 20-week pilot randomized controlled trial (RCT) with a waitlist control crossover design aims to enroll 70 community-dwelling older adults with elevated depressive symptoms. The treatment group will receive the 10-week intervention immediately, whereas the waitlist control group will cross over and receive the intervention after 10 weeks. This pilot is part of a multiphase project involving a single-group feasibility study (completed in December 2022). This project consists of a pilot RCT (described in this protocol) and an implementation feasibility study running in parallel with the pilot RCT. The primary clinical outcome of the pilot is the change in depressive symptoms after the intervention and at the 20-week postrandomization follow-up. Additional outcomes include acceptability, adherence, and changes in anxiety, social isolation, and quality of life.

**Results:**

Institutional review board approval was obtained for the proposed trial in April 2022. Recruitment for the pilot RCT began in January 2023 and is anticipated to end in September 2023. On completion of the pilot trial, we will examine the preliminary efficacy of the intervention on depression symptoms and other secondary clinical outcomes in an intention-to-treat analysis.

**Conclusions:**

Although web-based cognitive behavioral therapy programs are available, most programs have low adherence and very few are tailored for older adults. Our intervention addresses this gap. Older adults, particularly those with mobility difficulties and multiple chronic health conditions, could benefit from internet-based psychotherapy. This approach can serve a pressing need in society while being cost-effective, scalable, and convenient. This pilot RCT builds on a completed single-group feasibility study by determining the preliminary effects of the intervention compared with a control condition. The findings will provide a foundation for a future fully-powered randomized controlled efficacy trial. If our intervention is found to be effective, implications extend to other digital mental health interventions and populations with physical disabilities and access restrictions who face persistent disparities in mental health.

**Trial Registration:**

ClinicalTrials.gov NCT05593276; https://clinicaltrials.gov/ct2/show/NCT05593276

**International Registered Report Identifier (IRRID):**

PRR1-10.2196/44210

## Introduction

### Background

Depression in older adults has serious consequences, including worsened physical health and chronic disease progression [1-3], increased functional limitations and disabilities [4,5], institutionalization [6], and premature mortality due to comorbid conditions and suicide [7,8]. Low-income and homebound older adults are especially at high risk for experiencing depression. In one US representative sample, estimates for rates of depression in homebound older adults were approximately 40% [9]. Further complicating this burden of depression is a recent steep increase in the number of homebound older adults, likely in part driven by COVID-19 [10].

Although evidence-based pharmacological and nonpharmacological treatments exist, not all options are readily accessible to all populations of older adults [11]. Low-income and homebound older adults face significant access barriers to mental health treatments due to mobility, transportation, and financial difficulties. In addition, few providers have specialized training in working with older populations [12,13]. Given the lack of service providers, high rates of depression in specific subpopulations of older adults, and demographic trends toward a higher number of homebound older adults, interventions that are both accessible and scalable are urgently needed.

Digital mental health interventions have the potential to address the gaps in mental health treatment faced by low-income and homebound older adults. Affirming this, a recent national panel of expert stakeholders recommended that digital mental health interventions be broadly adopted and that insurers expand their coverage and reimbursement [14]. Cognitive behavioral therapy (CBT) is an evidence-based form of psychological treatment and has been adapted to multiple age groups [15-17] as well as medical and social contexts [18,19]. CBT is well suited for digital-based delivery, given its highly structured format and skill-based learning [20]. Hundreds of clinical trials have taken place in the last decade to test internet-delivered CBT (iCBT) and presented robust findings supporting the acceptability and effectiveness of this treatment modality [21-25]. iCBT is convenient and self-paced, less expensive than traditional psychotherapy, and scalable due to content delivery automation.

Research has consistently shown that tailoring treatment to specific populations, contexts, and settings is associated with increased uptake, acceptability, and sustainability [26,27]. In the case of older adults, procedural and content modifications to CBT have been discussed that incorporate differences in thinking styles in older adults and age-related adjustments [28]. However, when packaged for internet delivery, empirically supported iCBT programs often employ a one-size-fits-all approach, and very few have been designed to consider the needs of older adults [29-31]. In general, older adults are underrepresented in iCBT trials. A review found that only 3% of iCBT trial participants were older adults [32]. Since then, older adults’ participation has increased. However, a recent systematic review found that older adults are still largely under-represented as participants in rigorously designed studies [25].

Recent studies involving homebound older adults have shown that modifications to both contents (eg, adding aging-related themes) and web interface (website or app) are needed to improve adherence and engagement with iCBT [33,34]. These studies suggest that older adults had difficulty applying lessons when presented with content that failed to address aging-related topics and were less tolerant to poor usability issues, possibly due to a combination of age-related changes (eg, cognitive, vision, motor control, speech, and hearing), physical disabilities, and their lack of familiarity with modern technology. Most well-established iCBT programs contain a large amount of text, are highly didactic, and are hosted on interfaces that are not age-friendly (eg, small text and buttons). Usability issues and technical challenges are frequently reported, which can lower adherence and ultimately reduce treatment effects. The lack of tailored solutions may be more problematic for homebound older adults, who tend to be older, less tech-savvy, have more cognitive and functional limitations, and are more likely to experience usability issues [35].

### Objective

The primary aim of this study is to evaluate the efficacy of a 9-session iCBT program in treating depression in low-income homebound older adults. Additional outcomes and potential covariates will be captured, including anxiety, loneliness, and health-related quality of life.

A lack of iCBT products suitable for homebound older adults reflects and contributes to the digital divide experienced by them. Barring treatment innovation, older adults will continue to be left behind and face persistent mental health disparities related to access. This study aims to fill this void by testing the preliminary effects of a novel iCBT program designed for homebound older adults.

### Intervention Model

Empower@Home is an iCBT program designed to treat the core symptoms of depression in older adults. It consists of 9 web-based sessions grounded in CBT principles and homework assignments (ie, weekly practices) made available over 10 weeks. Each lesson is presented as a series of short videos with voice-overs that include didactic text, images of diverse older adults, inspirational quotes, and interactive exercises. Sessions are written at an eighth-grade reading level, and all spoken content is captioned. The weekly home practice tasks are modest and typically require 20 minutes or less of commitment from the user. A workbook with summarized session content and home practices is also provided to participants.

The sessions are enhanced with an animated case story series featuring a 74-year-old homebound woman named Jackie. The animated story is embedded within each session, like an episode of a television show. This content serves to reinforce core skills and techniques taught. Prior research has found that including short multimedia entertainment is a useful approach for communicating learning objectives in psychoeducational materials [36].

The session scripts of Empower@Home were developed by a team of researchers, clinicians, older adults, and social service providers via a co-design process. The web platform that delivers Empower@Home is a custom learning management system built using state-of-the-art, agile development processes. All interface features are compatible with accessibility standards and current best practices for making an age-friendly user interface and experience design [37]. For example, the main user interface features large buttons, text, icons with text descriptions, high-contrast color schemes, and intuitive navigation.

Informed by the Efficiency Model of Support [38], support from trained laypersons called Empower Coaches supplements the core web-based sessions of Empower@Home. Human support aims at increasing a participant’s ability to use the technology to obtain the intended treatment outcome [38]. Previous studies have shown that supported iCBT is more effective and associated with better adherence than unsupported interventions [39-41]. However, support mechanisms are generally underspecified and understudied, and it is not entirely clear what type and intensity of support are needed for homebound older adults to engage in iCBT successfully.

Informed by our previous research and the Efficiency Model of Support, we provide weekly check-ins with a supportive guide (ie, Empower Coach). The weekly check-ins are Coach-initiated contacts designed to prevent and address potential failure points, including engagement, working knowledge of the iCBT platform, and implementation of iCBT. All weekly check-ins are telephone-based. The Empower Coaches are laypersons without specialized mental health training or independent clinical licensure. The support content includes simple feedback, encouragement, homework review, and assistance with self-help tools without additional traditional therapy. Coaching sessions are highly individualized to meet the particular needs of the participants. On the basis of participants’ preferences, they may use the weekly check-in sessions to go over the web-based program with their coaches, whereas others complete the web-based portion on their own before the phone-based check-in sessions. Coaching sessions can range from 5 minutes to an hour per week, depending on the participants’ needs and preferences.

Coach training involves reviewing all web-based sessions of Empower@Home (takes approximately 4-5 hours to complete), a self-directed asynchronous web-based training (approximately 1.5 hours), and a synchronous training workshop (approximately 3 hours). The total training burden is approximately 9-10 hours per coach.

## Methods

### Preliminary Study

The procedures described in this protocol, including recruitment, assessments, coaching calls, and device shipments and returns, have been tested in a completed single-group uncontrolled feasibility study. Findings from the single-group study have not yet been published, but preliminary analysis shows that the intervention is feasible and acceptable, with high satisfaction ratings, and is associated with significant within-group reductions in depressive symptoms and several secondary clinical outcomes. Study procedures for the pilot randomized controlled trial (RCT) are refined based on lessons learned from the feasibility pilot.

### Study Setting and Aims

The study will be managed from the University of Michigan in collaboration with community agencies serving older adults. Participants will reside throughout Michigan in both rural and urban areas. All participants will be 60 years or older and are expected to be predominantly low income. Participants will complete the intervention in their own homes, with all assessments and technological support provided remotely by phone.

### Eligibility Criteria

To be eligible for the trial, participants must be at 60 years or older and have at least mild depression (score of ≥8 on the Patient Health Questionnaire-9 [PHQ-9]). Participants will be excluded if they (1) have probable cognitive impairment based on the Blessed Orientation-Memory-Concentration Test (score ≥10), (2) do not speak English, (3) have moderate to high risk of suicide based on the Columbia-Suicide Severity Rating Scale, (4) have a terminal illness or are in unstable physical health with a high risk of repeated hospitalizations within the next 3 months, (5) have a visual impairment based on self-reported inability to use a screen with correction, (6) have a current or recent history of substance use based on a score of ≥2 on the CAGE-AID Substance Abuse Screening Tool, (7) have a psychotic disorder based on self-report, or (8) are currently receiving psychotherapy. The study will not exclude participants based on racial or gender identification. Completing the intervention will require a tablet and internet accessibility. Participants are not required to have a computer or internet access; those who lack 1 or both resources will be provided a tablet and access to the internet at no cost during the active intervention period.

### Recruitment and Compensation

Participants will be recruited into the study on a rolling basis and will be drawn from multiple community agencies as well as other public places, including social media and local news outlets. The social service agencies that participated in this study’s intervention development and implementation feasibility phase were predominantly Area Agencies on Aging based throughout Michigan. These agencies serve older adults by offering services to enable their clients to maintain independence. These services may involve case management, caregiver services, and meals on wheels. These agencies will refer participants to the study based on their judgment of the appropriateness of the intervention for their clients.

After receiving referrals, study personnel will contact potential participants via phone to screen for eligibility. The initial screening is expected to take 20 minutes to complete. Participants will provide recorded verbal consent. Those who decline to participate will be referred back to their case managers or agency when possible. Advertisements placed via social media (eg, Facebook and Nextdoor) and through research registries will also allow participants to self-refer and be screened for eligibility.

Those who qualify for the trial will be paid up to US $100. Compensation is determined based on the number of assessments completed. Partial compensation is available (eg, participants who complete only the baseline assessment will receive US $30).

### Study Design

Eligible and consented participants will be assigned either to an active treatment or a waitlist condition group that will cross over to the intervention at 10 weeks. A computer-generated random sequence will be used for assignment into either condition at a ratio of 1:1. Given the content of the intervention and study design, blinding the participant and evaluator to the condition will not be feasible.

All participants will be assessed using the same schedule. All will be invited to complete the comprehensive baseline assessment, postintervention or control assessment at week 10, and a follow-up assessment at week 20. Participants on the waitlist control will receive the intervention after their post-test at week 10 (Figure 1).

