### Clinical Management and Storage

All data related to the study (screening, pretest, coaching sessions, posttest, and follow-up) will be entered directly by project staff into REDCap [42]. During the active intervention, participants will be asked to fill out the PHQ-9 every other week, administered as a part of the web-based therapy lesson. These assessment data are stored in a HIPAA (Health Insurance Portability and Accountability Act)–compliant database hosted by the University of Michigan.

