### Measures

All measures are presented in Table 1. The primary clinical outcome in the study will be depressive symptoms as measured by the PHQ-9. The PHQ-9 is widely used in clinical research and has been used to evaluate older adults with medical and psychiatric illnesses in and outside of health care settings [43,44]. The PHQ-9 has been found to perform comparably to the Geriatric Depression Scale in identifying depression in older adults [45]. Scores on the PHQ-9 can range from 0 to 27 and indicate minimal, mild, moderate, moderately severe, or severe depression symptom severity. Sample items include “In the last week, have you had little interest or pleasure in doing things?” and “In the last two weeks, have you been feeling down, depressed, or hopeless?” Respondents indicate answers on a 4-point Likert scale ranging from “not at all” to “nearly every day.” In primary care patients, the measure has a sensitivity of 88% and a specificity of 88% [43]. The PHQ-9 will be administered at initial screening, baseline, after intervention, and 20-week follow-up. In addition, participants will complete a PHQ-9 self-assessment built into the web-based sessions every other week. To mimic the additional assessment patterns in the treatment group, participants in the control condition will also be administered the PHQ-9 every other week via phone during the 10-week waiting period.

**Table 1 table1:** Study measures and time points.

Variable	Assessment or activity	Screening	Baseline	Postrandomization			Follow-up
				Biweekly	Post		
Depression	PHQ-9^a^	✓	✓	✓	✓	✓	
Anxiety	GAD-7^b^		✓		✓	✓	
Social isolation	PROMIS-SI 8a^c^		✓		✓	✓	
Health self-assessment	PROMIS-GH^d^		✓		✓	✓	
Well-being and quality of life	EQ-5D-5L		✓		✓	✓	
Skill acquisition	CBTSQ^e^		✓		✓	✓	
Acceptability	Modified TEI^f^				✓		
Adherence	Session completion				✓		
Participant background	Sociodemographic, health status, and physical functioning	✓	✓				

^a^PHQ-9: Patient Health Questionnaire-9.

^b^GAD-7: Generalized Anxiety Disorder-7.

^c^PROMIS-SI 8a: Patient-Reported Outcomes Measurement Information System–Social Isolation 8a.

^d^PROMIS-GH: Patient-Reported Outcomes Measurement Information System–General Health.

^e^CBTSQ: Cognitive-Behavioral Therapy Skills Questionnaire.

^f^TEI: Treatment Evaluation Inventory.

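### The reason given for leaving the evaluator unblinded does not show why the person asking the week-10 PHQ-9 by phone must know the allocation

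*Protocol article*

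**What the plan says.** All references are to the protocol article.

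- **Blinding (Study Design).** "Given the content of the intervention and study design, blinding the participant and evaluator to the condition will not be feasible". No separate reason is given for the evaluator.
- **Schedule (Study Design).** "All participants will be assessed using the same schedule": baseline, week 10 and week 20. The waitlist arm receives the intervention after its week-10 post-test.
- **Mode (Study Setting and Aims).** Participants take part from home, "with all assessments and technological support provided remotely by phone".
- **Data entry (Clinical Management and Storage).** Screening, pretest, coaching, posttest and follow-up data "will be entered directly by project staff into REDCap".
- **Primary outcome (Measures).** "The primary clinical outcome in the study will be depressive symptoms as measured by the PHQ-9". On timing: "The PHQ-9 will be administered at initial screening, baseline, after intervention, and 20-week follow-up".
- **Interim PHQ-9 (Measures).** In the treatment arm, "participants will complete a PHQ-9 self-assessment built into the web-based sessions every other week". In contrast, "participants in the control condition will also be administered the PHQ-9 every other week via phone during the 10-week waiting period".
- **Limitations (Strengths and Limitations).** The small sample and the waitlist control are named as possible sources of overestimated effects. Unmasked outcome assessment is not mentioned.

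**The concern.** The PHQ-9 is a subjective outcome, and at week 10 the article has it administered in a remote assessment. An interviewer who knows the arm can influence the answers through tone, prompting or handling of hesitant replies. The participant may also answer more favourably to someone connected with the programme. If this works in the intervention's favour, it adds to the estimated effect, and no analysis of the trial's own data can separate the two.

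The article takes care elsewhere to balance non-specific influences. The control arm has a comparable amount of phone contact and a matching frequency of PHQ-9 assessment. An assessor who knows the arm works against that effort. The results are also meant to inform a later fully powered trial, so an inflated estimate would be carried into its planning.

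**Working it through.** **1. Does the stated reason cover the week-10 assessor?** No planned figure depends on masking, so this part is a reading of the text. The possible routes by which the design could force the assessor to know the arm are these:

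| Possible route | What the article says | Does it force unmasking at week 10? |
|---|---|---|
| Visible cues at a visit | Assessments are remote, by phone | No |
| Different timing by arm | One schedule for both arms | No |
| Crossover reveals the arm | Crossover follows the week-10 post-test | No |
| Contact in one arm only | Companionship calls give the control arm comparable phone contact | No |
| Treatment-specific questions | Table 1 puts the modified Treatment Evaluation Inventory (TEI) at the Post time point | Only if asked before the PHQ-9, or if its presence on the form reveals the arm |
| The assessor is also the coach or caller | Not stated | Only if roles overlap |
| The participant mentions the programme | Always possible | Sometimes |

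The last three routes can be reduced by assigning calls and ordering questions. None follows from the content of the intervention.

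**2. Which measurements are affected?** The Sample Size section uses seven PHQ-9 measurements: baseline, five interim (about weeks 1, 3, 5, 7 and 9) and week 10. In the treatment arm the five interim scores are self-completed on the web, so no interviewer is involved. After baseline, the only measurement in that comparison that staff administer in the treatment arm is week 10. The control arm's interim scores are taken by phone. That difference in mode is a separate matter, and masking the week-10 assessor would not change it.

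**3. Illustrative size.** The documents give no value for interviewer bias, so a difference *b* between arms at week 10 is assumed.

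- Target effect: 0.8 × 5 = 4 points over 10 weeks (Sample Size).
- Share of target: 0.5/4 = 12.5%; 1/4 = 25%; 1.5/4 = 37.5%.

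*Simple comparison of change from baseline to week 10.* Inputs are the SD of change of 5 and 35 per arm with 20% attrition, so 35 × 0.8 = 28 per arm. A two-sided test is assumed, since the article gives α = .05 without sidedness.

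SE = 5 × √(2/28) = 1.34.

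Rejection probability with no true effect = Φ(b/SE − 1.96) + Φ(−b/SE − 1.96):

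| Assumed b (points) | Probability of rejection (nominal 5%) |
|---|---|
| 0.5 | 6.6% |
| 1.0 | 11.6% |
| 1.5 | 20.2% |

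*Seven-point linear slope, as in the Sample Size section.* With times 0, 1, 3, 5, 7, 9 and 10, the mean is 35/7 = 5. The sum of squares is 25 + 16 + 4 + 0 + 4 + 16 + 25 = 90. With complete data and simple least squares, the week-10 value has weight (10 − 5)/90 = 5/90 in the weekly slope. Over 10 weeks, 10 × 5/90 = 0.56 of a bias confined to week 10 reaches the estimated difference. So 0.5 to 1.5 points become 0.28 to 0.83 points, and 0.28/4 = 7%, 0.83/4 = 21% of the target.

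**The case against.** The strongest reply has four parts.

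**The rater is really the participant.** The PHQ-9 is a fixed-item self-report with four response options, and participants know their arm. Masking the interviewer cannot remove their own reporting bias. This stands, and it limits the gain to interviewer influence.

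**Staffing is not described.** The article does not say who makes the week-10 and week-20 calls, how many staff there are, or whether assessors are separate from coaches. It names no companionship-caller role. The same broad group, project staff, enters both coaching and outcome data. This also stands: that existing staff could be masked is an assumption. A reader might infer that coaches collect the primary outcome from their own participants, but the article neither says nor excludes this. Call assignment and question order are details an article may leave to the full protocol, so their absence is not the fault. The fault is the explicit statement that the evaluator cannot be blinded, with a reason that does not reach the evaluator.

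**Not every PHQ-9 is a staff phone call.** The general statement in Study Setting and Aims might suggest that all primary-outcome data come from staff who know the arm. The Measures section rules this out for the treatment arm's interim scores.

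**Week 20 is different.** By then both arms have been offered the intervention, so a bias towards the intervention is much less obvious. The case rests mainly on week 10.

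It is also fair to say that the lack of blinding is openly disclosed, and that this is a pilot whose limitations section already warns of overestimation from other causes.

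**Conclusion.** The point holds in a limited form. The article treats participant and evaluator blinding as one problem, and the reason it gives does not justify an unmasked assessor for the week-10 phone PHQ-9. Week 20 is affected with less at stake, and the treatment arm's interim web scores are not affected.

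The size is unknown. The figures above show only what an assumed bias of 0.5 to 1.5 points would do: 12.5% to 37.5% of the target in a simple week-10 comparison, about 7% to 21% in the planned seven-point slope. They rest on that assumed range, on a bias favouring the intervention and, for the slope, on complete data with the bias confined to week 10. They are not evidence that such a bias will occur. The planned sample size and nominal α do not change.

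This is a worthwhile low-cost improvement. It does not invalidate the trial, and it does not justify a dedicated extra assessor.

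**What to change.** Reword the blinding statement in Study Design so that only participants and those delivering coaching or companionship calls are declared unblindable. Then, using existing project staff:

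- Have the week-10 call, and where practical the week-20 call, made by someone who does not coach or make companionship calls to that participant and who is not shown the allocation.
- At the start of the call, ask the participant not to mention their programme or calls.
- Ask the PHQ-9 first, and the TEI and session questions last.
- Record whether the assessor became unmasked.

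If existing staffing cannot support this, say so in Study Design as the reason, and add unmasked outcome assessment to Strengths and Limitations.

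The cost is a change of wording, some scheduling so that staff exchange participants, and keeping the allocation out of the assessor's view in REDCap. Some calls will still be unmasked by participants. Sample size, assessment schedule and treatment are unaffected.
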